### Secondary Outcomes

A range of secondary outcomes were collected in each survey wave, including (1) child anthropometric outcomes, including child height, weight, and anemia status for all children born after the start of the intervention; (2) sexual and marital well-being; (3) women’s anthropometric outcomes, including height, weight, and anemia status; (4) women’s and children’s educational attainment, including time spent in school, type of school (public or private) attended, and the highest educational qualification achieved; (5) work, income, and women’s employment, including women’s time use (time spent on child care vs household and income-generating activities) and sources of household income; (6) household assets and wealth, including changes in asset ownership over time; and (7) expenditures, in particular changes in food expenditures and durable expenditures over time.

Outcomes were collected according to the schedule outlined in Table 2. All survey instruments (baseline and follow-up) and intervention-monitoring tools to track participants and intervention uptake over the course of the study are available upon request.

**Table 2 table2:** Outcome measures and instruments.

Outcomes and instruments	Baseline	Follow-up, year 1	Follow-up, year 2
Attitude and knowledge of family planning	✓^a^	✓	✓
Contraceptive use	✓	✓	✓
Pregnancy and fertility outcomes	✓	✓	✓
Child anthropometry (height, weight, and anemia)	—^b^	✓	✓
Women’s anthropometry (height, weight, and anemia)	✓	✓	✓
Educational attainment	✓	✓	✓
Formal and informal employment	✓	✓	✓
Women’s time use (primary and secondary activities)	✓	✓	✓
Household income and expenditure	✓	✓	✓
Household assets	✓	✓	✓
Baseline survey	✓	—	—
Year 1 follow-up survey	—	✓	—
Year 2 follow-up survey	—	—	✓

^a^✓: indicates that data on that outcome were collected in the indicated survey wave.

^b^–: indicates that data on that outcome were not collected in the indicated survey wave.

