### Study Objectives

To address these gaps in the evidence, we conducted a randomized controlled trial to identify the causal impact of improved access to PPFP. The study population included married postpartum women aged 18 to 35 years in Lilongwe, Malawi. As part of the trial, each woman in the study was randomly assigned to either the treatment or control arm. A woman who was assigned to the intervention arm received a 2-year–long family planning intervention that was designed to reduce key barriers to access for postpartum women in urban Malawi [14,15]. The primary objective of this study is to evaluate the impact of the family planning intervention on contraceptive use, fertility, birth spacing, and other measures of maternal and child health and well-being in postpartum women who received the family planning intervention (the intervention arm) compared with women who did not receive the intervention (the control group). Primary outcomes include short-term outcomes related to modern contraceptive use and contraceptive method mix (the profile of the relative level of use of different contraceptive methods within our study sample) as well as intermediate outcomes related to fertility and birth spacing. Shorter-term secondary outcomes include changes in desired fertility, unmet need for family planning, and outcomes associated with maternal and child health, including safe pregnancy, birth height and weight, and nutritional status. Longer-term secondary outcomes include educational attainment (matriculation rates and years of schooling completed), labor market outcomes (employment status, female labor supply, and women’s time use), and income. This study seeks to fill the current knowledge gaps on the effectiveness of family planning interventions by directly identifying the impact of an increase in access to family planning on fertility and health outcomes. A downstream objective of this study is to demonstrate that the benefits of improving access to family planning are likely to extend beyond the health domain by also improving well-being and contributing to the alleviation of poverty.

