**Figure 1 figure1:**
[figure not shown]
Experimental framework and flowchart.

For the study, we recruited women who, at the time of the baseline survey, (1) were married, (2) were either currently pregnant or had given birth within 6 months from the time of the baseline screening, (3) were between the ages of 18 and 35 years, and (4) lived in the city of Lilongwe. Women who successfully met these criteria and consented to participate in the study were recruited. In addition, no 2 eligible women were enrolled from the same household. If multiple women from the same household were potentially eligible to be recruited based on the 4 inclusion criteria above, the youngest eligible woman from the household was chosen to participate—given that randomization was to be administered at the individual woman level, it was necessary for us to select only 1 eligible woman from a household to minimize any possible contamination across women in the intervention and control groups. We also ensured that eligible women who were selected for the study were sufficiently distant (at least five households apart) from each other, which also served to reduce any spillover effects between treated and control women who lived in the same neighborhood. Following the recruitment of women, 1 member from the recruited woman’s household was identified and selected to respond to sections in the baseline and follow-up surveys that inquired about household expenditures, assets, and consumption. The household member selected for this part of the study was required to meet the following inclusion criteria: (1) he or she was >18 years old, (2) he or she was a resident of the same household from which the woman respondent described above was selected, and (3) he or she claimed to be knowledgeable about the household’s financial status, consumption, and expenditure. The household member who successfully met these inclusion criteria and who consented to participate in this part of the study was recruited to participate. Finally, children in the household were recruited to complete an anthropometric module, including data collection of height, weight, and anemia status at baseline and again at the 2 follow-ups. The children who were selected from the household for this part of the study (1) were aged <6 years, (2) were identified as the biological or adopted children of the woman who was recruited for the main part of the study, and (3) resided in the same household as the eligible woman. Children who successfully met these inclusion criteria and whose mothers consented to them participating in this part of the study were recruited to participate.

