### Primary Outcomes

At the designated 1-year and 2-year follow-up periods, the entire study sample of women was resurveyed to create a panel of individual women in which each woman and household would be observed over 3 time periods. In each follow-up round, we collected survey data on a range of primary outcomes of interest, which include (1) contraceptive use, including changes in contraceptive prevalence, changes in method mix, and adherence to methods (compliance and discontinuation) and (2) fertility and birth spacing outcomes, including pregnancy status, parity, and time since the last birth.

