### Fertility (Number of Children Per Woman)

Similarly, we use fertility estimates for Lilongwe from the 2010 Malawi DHS and assume a baseline fertility rate of 4.5 births per woman in the sample at baseline. To infer a potential effect size, we again look to evidence from the Navrongo and Matlab studies, both of which found a total reduction of 1 birth per woman (equivalent to a 15% decrease in their respective baseline fertility) among women in their respective intervention arms over their respective study periods [9,23]. In recognizing that both the Matlab and Navrongo studies were larger-scale, cluster-randomized designs with longer follow-up periods, we estimate that we will only be able to observe differences of 0.5 births. Our power calculations show that we will have 99% power to detect a 0.5 birth per woman decrease, equivalent to a 12% decrease in fertility, in the intervention arm from 4.5 children per woman to 4.0 children per woman, assuming an attrition-adjusted sample of 1460 women (730 women in each arm) by end line.

Table 4 presents the levels of power 1-ß that will be achieved for various minimum effect sizes for fertility (ie, the difference in the average number of children per woman between the intervention and control arms at end line), assuming a baseline fertility of 4.5 children per woman in both intervention and control arms, a standard deviation of 2 children per woman for both arms, and a fixed end-line sample size of 1460 women (730 in each arm).

Finally, robustness checks (5% and 10% sample truncations and coarsening of independent variables) and falsification tests, which include placebo regression, simulation, and resampling methods, will be conducted to ascertain the strength and significance of our estimates. We will also conduct attrition-adjusted analyses to assess the extent of differential loss-to-follow-up outcomes.

**Table 4 table4:** Power calculations—fertility.

Control fertility, number of children per woman	Intervention fertility, number of children per woman	Significance level, α	Control sample size	Intervention sample size	Power
4.5	3.5	.05	730	730	1
4.5	4.0	.05	730	730	0.99
4.5	4.2	.05	730	730	0.89
4.5	4.3	.05	730	730	0.61

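### The stated child growth and anemia group mixes children already conceived at baseline with children conceived after randomisation; for the latter, an arm difference cannot be read as an effect on child health

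*Protocol article*

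**What the plan says.** Under Secondary Outcomes, the first item is "child height, weight, and anemia status for all children born after the start of the intervention". In Table 2, in the same section, the row "Child anthropometry (height, weight, and anemia" carries a dash at baseline, and the footnote explains that a dash means the data were not collected in that wave.

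Two other sections describe a wider group. Study Sample and Inclusion Criteria says that the woman's biological or adopted children under 6 years living with her were recruited to an anthropometric module, "including data collection of height, weight, and anemia status at baseline and again at the 2 follow-ups". Survey Instruments and Monitoring Tools includes child anthropometry for children under 6 in the baseline visit.

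The intervention is meant to change childbearing. The Primary Outcomes section lists "fertility and birth spacing outcomes, including pregnancy status, parity, and time since the last birth", and the fertility power section states "we will have 99% power to detect a 0.5 birth per woman decrease". Women were eligible if they were pregnant or had given birth within the previous 6 months. The Analysis Plan applies one intent-to-treat regression on assigned arm to the immediate, intermediate and long-term outcomes, and names no step for selection into birth.

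**The concern.** Randomisation makes the two groups of women comparable. It makes their children comparable only where arm could not influence whether the child was conceived. The stated group contains two kinds of child:

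- **In utero at baseline.** Conception came before randomisation, so the arms stay comparable on this point.
- **Conceived after randomisation.** If the intervention works as intended, fewer such children exist in the intervention arm, and their mothers may differ from the control mothers in wealth, parity, birth interval or fertility intention.

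A third kind, the child born shortly before baseline to a woman recruited postpartum, falls outside the wording although selection into conception does not affect it.

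Child health belongs to the study's stated objective, and the trial sets out to identify causal effects. An arm difference in height or anemia among later-conceived children could reflect who went on to give birth. It could also be masked if the selection runs the other way. Arm also changes the mix of the two kinds of child, and with it the children's age at measurement.

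**Working it through.** **1. The plan's own figures: does it expect the intervention to change births?**
Inputs from the fertility power section: 4.5 v 4.0 births per woman, "a standard deviation of 2 children per woman for both arms", 730 women per arm, alpha .05. The Analysis Plan specifies one-sided tests.

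Standard error = 2 × √(2/730) = 0.1047. Power = Φ(difference/0.1047 − 1.645).

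| Intervention fertility | Difference | Computed | Table 4 |
|---|---|---|---|
| 3.5 | 1.0 | 1.000 | 1 |
| 4.0 | 0.5 | 0.999 | 0.99 |
| 4.2 | 0.3 | 0.889 | 0.89 |
| 4.3 | 0.2 | 0.605 | 0.61 |

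Table 4 reproduces one-sided. It says nothing about child growth, for which the article gives no power figure. It does show that the design expects arm to alter how many children are born.

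**2. Size of the selection effect, with no true effect on any child.**
Let q be baseline-pregnancy births per woman, r_C and r_I the later-conceived births per woman in each arm, and g the gap in SD between averted children and all others.

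Spurious difference = [(r_C − r_I)/(q + r_C)] × g. For later-conceived children alone, set q = 0.

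None of these inputs is in the documents. The assumed values are r_C = 0.25, r_I = 0.20, g = 0.5 SD.

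| Group | Calculation | Spurious difference |
|---|---|---|
| Later-conceived only | 0.05/0.25 × 0.5 | 0.10 SD |
| Whole stated group, q = 0.3 | 0.05/0.55 × 0.5 | 0.045 SD |
| Whole stated group, q = 0.5 | 0.05/0.75 × 0.5 | 0.033 SD |
| Whole stated group, q = 0.7 | 0.05/0.95 × 0.5 | 0.026 SD |
| In utero at baseline only | no births averted | 0 from this mechanism |

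If the averted children would have been taller than the rest, g is negative and the sign reverses.

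**3. Wider assumed range.**
Take q from 0.3 to 0.7, r_C from 0.2 to 0.4, 12% to 50% of later births averted, and g from 0.2 to 0.5 SD. The false-positive rate is 1 − Φ(1.645 − difference/SE), with SE = √(1/n_C + 1/n_I). The n are child counts from 730 women per arm, treated as independent.

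- Whole stated group, smallest: 0.2 × 0.12/0.9 × 0.2 = 0.005 SD; false-positive rate about 6%.
- Whole stated group, largest: 0.4 × 0.5/0.7 × 0.5 = 0.14 SD; about 67%.
- Later-conceived only: 0.12 × 0.2 = 0.024 SD to 0.5 × 0.5 = 0.25 SD; about 7% to 79%.

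The nominal rate is 5%. The width of the range reflects how little the documents fix.

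**4. Change in mix.**
With q = 0.5 and the step 2 inputs, later-conceived children are 0.25/0.75 = 33% of the control group and 0.20/0.70 = 29% of the intervention group. The arms would thus differ in age distribution, which is one reason to adjust for age.

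**The case against.** The strongest reply is that the Secondary Outcomes sentence lists data collected in each wave and does not define an analysis set. Two other sections describe measuring all children under 6 from baseline, and the Analysis Plan foresees effects for older children. A reader might infer that later-born children are the only ones compared. The documents do not support that: they conflict on which children were measured. What stands is that the sentence is the article's statement of the child outcome, and it names this group.

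A reader might also infer that the whole child comparison has lost its randomised basis. That goes too far, because children in utero at baseline belong to the stated group and are free of this selection. For the same reason, 0.10 SD must not be read as the error in the whole group.

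It can be said that a separate pre-analysis plan, which the article mentions, may handle selection. It may, so the absence of a selection step in the article is weak evidence that none exists. The population, however, is stated in the article itself. The attrition-adjusted analyses that the article describes address loss to follow-up, not children who were never conceived.

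Study Objectives also lists "safe pregnancy, birth height and weight, and nutritional status". Those outcomes would share the problem if taken over all later births, but the article states no population for them, so nothing is claimed there.

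Finally, Table 2 need not be the wrong side of the baseline conflict. Its dash is consistent with an outcome confined to children born after the start.

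**Conclusion.** The concern holds for children conceived after randomisation: the intervention is designed to change whether they exist, and a regression on arm does not remove that selection. It does not extend to children in utero at baseline. The stated group blends the two and, as worded, omits already-born index children.

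On the assumed inputs, the spurious difference is 0.10 SD among later-conceived children and about 0.03 to 0.05 SD over the whole stated group. The size rests entirely on assumptions, and the sign could go either way.

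The contradiction over baseline child measurement is real, and the documents do not show which side is correct. The child outcome is one of several secondary outcome groups. The primary outcomes, and the power for contraceptive prevalence and fertility, are unaffected.

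**What to change.** 1. Make the main child analysis the index child, already born or in utero at baseline, compared by the mother's assigned arm. Adjust for age and sex and, for children already born, for the baseline measurement if it was taken. No baseline value can exist for children in utero.
2. Apply the attrition-adjusted analyses planned for the women. At year 2, 1669 of 2143 women (77.88%) were reinterviewed, and pregnancy loss and child death also occur after randomisation, so this analysis will not include a child from every randomised woman.
3. Report children conceived after randomisation separately, either as descriptive or with selection bounds.
4. Reconcile Table 2 with Study Sample and Inclusion Criteria and with Survey Instruments and Monitoring Tools by checking what was collected at baseline, without presuming which is right.

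The cost is analysis wording and a correction on whichever side of the conflict is wrong. It needs no new data if children under 6 were measured as those two sections describe. The article reports analysis as still under way. The downside is that the main child estimate would no longer speak directly to later-born children.

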### Survey Instruments and Monitoring Tools

A paper version of the baseline survey instrument, which served as a template for all follow-up surveys, is provided in Multimedia Appendix 1. Before administering the survey, we explained the purpose of the study to respondents and asked for their consent using the study consent forms. Baseline surveys, anthropometric measurements, and related study activities (eg, discussion of anthropometric and anemia test results) were administered in a private room in the woman’s place of residence and lasted approximately two hours overall (75 min for administering the child anthropometry and woman questionnaire to the woman and her children aged <6 years and 45 min for administering the household questionnaire to the financially knowledgeable respondent). Short breaks of 5 to 10 min were given to the respondents at the end of each section, and additional breaks were taken at the request of the participant and at other scheduled times (eg, mealtime, picking children up from school, etc) as needed. Surveys were conducted in Chichewa, the local language, and followed the format of the survey questionnaire, which were electronically programmed into Android tablets. To successfully track our participants over time, we collected identifiable data, including names and contact information for each of the survey respondents (the woman, her children aged <6 years, and the financially knowledgeable member of the household), the names and background characteristics of other household members, the household address, contact phone numbers and emails, and GPS coordinates of the household. For the purpose of minimizing loss to follow-up, we took photographs of the household and of the survey respondents, and we asked respondents to provide the names and contact information of 2 contacts who did not live in the household and who could be contacted if the respondents could not be directly located in the follow-up period. To protect participant privacy and ensure confidentiality, all identifiable data are appropriately stored and secured in accordance with the data security measures described in the sections below.

The 1-year and 2-year follow-up surveys were administered in person to all women who continued to live in urban Lilongwe and who could be contacted within 3 contact attempts by the local field team. For women who either moved out of urban Lilongwe or who were unreachable after 3 contact attempts, the field team attempted to contact them by phone up to a maximum of 3 attempts; women who were reachable by phone within these 3 attempts were asked to participate in a short phone follow-up survey. To maintain a respondent’s privacy during an attempt to reach her by phone, the field enumerator conducting the call left no indication of the reason for the phone attempt (eg, voicemail, text message) on the respondent’s phone if there was no response to a call. To ensure that the respondent’s participation remained private, the field enumerator only continued with the phone call once she received assurance from the woman that she was able to speak on the phone without being overheard or interrupted. Any disruption or interruption during the phone call resulted in postponement or termination of the call. The phone follow-up survey instrument took no more than 20 min overall, and was an abbreviated version of the main in-person follow-up survey instrument. The aim of the phone survey was to maximize survey follow-up rates by attempting to include women who were physically unreachable. The only respondents who were recontacted for the phone follow-up survey were those respondents who were simply lost to follow-up. Respondents who had previously indicated that they were no longer interested in participating in the study were contacted.

The phone follow-up survey instrument consisted of abbreviated modules from the main in-person follow-up survey instrument. Before administering the phone survey, we explained clearly the purpose of the follow-up to respondents and asked for their consent to participate in the survey verbally over the phone. Following receipt of consent, we ensured confidentiality and privacy of responses by asking the respondent to find a private room or space where their responses could not be overheard by others. We proceeded with the phone survey only after having received confirmation from the respondent that her responses could not be overheard.

### Analysis Plan

Analysis of quantitative study data will be conducted using STATA and R (the R Project), where appropriate. A descriptive analysis will be performed for all variables, and unadjusted comparisons between experimental arms will be conducted. Descriptive statistics will be performed, including frequencies, means, and standard deviations. In addition, chi-square tests and one-tailed *t* tests will be used to examine associations in the data. A *P* value <.05 will be considered statistically significant for all statistical tests that are conducted. Given our hypotheses of the impact of our intervention on our key outcomes, one-sided hypotheses tests will be conducted for all our main analyses. Continuous variables will be tested for normality and nonnormal values will be categorized or transformed appropriately.

Our main econometric specifications will estimate the intent-to-treat (ITT) effect of our family planning intervention on fertility and other outcomes by directly regressing our outcomes of interest on a binary variable indicating receipt of the intervention. The main econometric specification for estimating the ITT effect of our family planning intervention is defined as follows:

where *Y_it_* is the outcome variable of interest for woman *i* in the period *t*=0,1,2 for baseline, 1-year follow-up, and 2-year follow-up, respectively; *T_it_* is an indicator of assignment to the treatment arm; *X_it_* is a vector of individual-level covariates that are controlled for in the analysis; *_i_* is the individual-specific fixed effect; *Y_i0_* is the baseline level of the outcome; and *ε_it_* is the error term. Here, the outcome variables of interest include immediate, intermediate, and long-term outcomes mentioned in the previous sections.

We will conduct several subgroup analyses to examine how the family planning intervention effects vary across particular subpopulations. Subgroups of interest include pregnant women, new mothers, women who have previously used family planning, women who expressed a desire to space or limit births at baseline, poorer women, and women with low educational attainment. In addition, we will estimate heterogeneous treatment effects for girls, older children, and high-parity households.

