### Sample Size and Power Calculations

The sample size of this study was powered to primarily identify the effect of using family planning on fertility; however, we will also examine the effects of the intervention on other maternal and child health outcomes of interest, in addition to key social and economic measures of well-being. On the basis of the preliminary power calculations for our primary outcomes of interest, a total of 2000 women were needed to be enrolled in the study. Of the women who were enrolled, the family planning intervention, baseline survey, and 2 follow-up surveys were administered to 1000 women (the treatment group), whereas a basic family planning information package, the baseline survey, and 2 follow-up surveys were administered to the other 1000 women (the control group).

Our target baseline sample consists of 2000 women who met the eligibility criteria and who consented to participate in the study. Previous research studies in Accra, Ghana, have found that 32% of initially screened women either did not meet the eligibility criteria or refused to participate [20-22]. Therefore, to meet our target sample size of 2000, we would need to screen 3000 households if we conservatively assumed a combined ineligibility or refusal rate of 32% from the screening. Of the 2000 women who were to be recruited into the study at baseline following the initial screening process, 1000 women were to be randomly assigned to the intervention arm and the remaining 1000 women were to be randomly assigned to the control arm. On the basis of prior study findings from Zambia [13], we expected an attrition rate of 27% in the sample over a 2-year study period, which would leave us with an attrition-adjusted sample size of 730 women in each treatment arm, or 1460 women overall, at the end of the 2-year study period.

Given this attrition-adjusted sample size, we have powered our study to detect effects in 2 key outcomes, namely changes in contraceptive prevalence and fertility, the latter measured by the number of births per woman.

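### A normality test may decide whether primary outcomes are categorised or transformed, so mean births, which the trial was sized on, could give way to a form chosen from the data

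*Protocol article*

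**What the plan says.** The first paragraph of the Analysis Plan covers descriptive statistics and unadjusted comparisons ("chi-square tests and one-tailed *t* tests will be used to examine associations in the data"), the significance threshold ("A *P* value <.05 will be considered statistically significant for all statistical tests that are conducted") and sidedness ("one-sided hypotheses tests will be conducted for all our main analyses"). It ends with the rule at issue: "Continuous variables will be tested for normality and nonnormal values will be categorized or transformed appropriately". The article names no normality test, transformation or cut-point, and exempts no outcome.

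The next paragraph gives the main intent-to-treat model as "directly regressing our outcomes of interest on a binary variable indicating receipt of the intervention". It has no normality step, and it does not say whether the rule applies there.

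The Primary Outcomes section includes "fertility and birth spacing outcomes, including pregnancy status, parity, and time since the last birth". The Sample Size section says the trial was powered on "changes in contraceptive prevalence and fertility, the latter measured by the number of births per woman". Table 4 defines the fertility effect as "the difference in the average number of children per woman between the intervention and control arms at end line", with control mean 4.5, SD 2 and 730 women per arm.

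**The concern.** A rule of this kind lets a data-dependent test choose the scale of the outcome. At this sample size it is also badly matched to its purpose. Comparing means in groups of about 800 does not need normal raw values, whereas a normality test at that size rejects for almost any small integer count or irregular distribution.

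Two things are at stake. First, a log, a square root or a category is a different quantity from the mean number of births in Table 4, and it cannot be read as births or months. Second, the word appropriately leaves the choice open. According to the Results, both follow-up surveys were complete and analysis was under way when the article was written, so a form chosen under this rule would be chosen with outcome data in hand. If that form is a category, power is also lost.

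**Working it through.** **Inputs from the article.** 730 women per arm, SD 2, control mean 4.5, and intervention means 3.5, 4.0, 4.2 and 4.3 (Table 4 and its text); alpha .05, one-sided (Analysis Plan); 1669 women reinterviewed at year 2 (Follow-Up Surveys); 1026 and 1117 women randomised.

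**Assumptions.** The article gives no distribution for births or birth spacing beyond the mean and SD, and no cut-points. The shapes and cut-points below are assumed and shown as ranges.

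**1. Reproduce Table 4.** SE = 2 × √(2/730) = 0.1047. One-sided power = Φ(δ/SE − 1.645).

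| δ (births) | δ/SE | One-sided power | Table 4 |
|---|---|---|---|
| 1.0 | 9.55 | 1.000 | 1 |
| 0.5 | 4.78 | 0.999 | 0.99 |
| 0.3 | 2.87 | 0.889 | 0.89 |
| 0.2 | 1.91 | 0.605 | 0.61 |

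Two-sided power would be 0.818 and 0.480 in the last two rows, which does not match. Table 4 is therefore a one-sided comparison of untransformed mean births.

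**2. Would a normality test reject at n = 1669?** Six shapes were simulated, 400 runs each: rounded normal (4.5, SD 2), Poisson 4.5, binomial with SD 2, 1 + Poisson(1.5), new births 0/1/2, and integer months 0-30. Shapiro-Wilk rejected in 100% of runs for every shape. The D'Agostino test rejected in 100% for all but the rounded normal, where it rejected in about 40%.

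**3. Is the rule needed?** Splitting 1669 in proportion to randomisation gives 1669 × 1026/2143 = 799 and 1669 × 1117/2143 = 870. For a skewed 0/1/2 birth count (assumed probabilities .75, .23, .02; 20,000 runs), the ordinary t test had type I error 0.048, both two-sided and one-sided. Non-normal raw values do not threaten validity here.

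**4. Cost of transforming.** One-sided t tests were simulated for three assumed count shapes, 730 per arm, 4000 runs each. Power with log(1+x) or square root was about 1.00 at 0.5 births, 0.88-0.92 at 0.3 and 0.59-0.67 at 0.2. Raw births in the same runs gave 0.999, 0.88-0.90 and 0.60-0.62. The change runs from a loss of about 3 points to a gain of about 5.

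**5. Cost of categorising.** Take births as a rounded normal, so P(births ≥ c) = 1 − Φ((c − 0.5 − mean)/2). One-sided power = Φ((d − 1.645 × SE0)/SE1), where d is the difference in proportions, SE0 uses the pooled proportion and SE1 the separate ones.

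Example: cut at 5 or more, 4.5 versus 4.2. The proportions are 0.500 and 0.440, so d = 0.0596, SE0 = 0.0261, SE1 = 0.0261, and power = Φ(0.638) = 0.738.

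| Cut | 0.5 births | 0.3 births | 0.2 births |
|---|---|---|---|
| ≥3 | 0.951 | 0.619 | 0.361 |
| ≥4 | 0.981 | 0.714 | 0.430 |
| ≥5 | 0.984 | 0.738 | 0.451 |
| ≥6 | 0.971 | 0.693 | 0.419 |
| ≥7 | 0.911 | 0.577 | 0.343 |
| Uncut | 0.999 | 0.889 | 0.605 |

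The loss depends on the assumed shape. For the three count shapes of step 4, cuts at 4 or 6 gave 0.95-1.00 at 0.5 births, 0.66-0.85 at 0.3 and 0.40-0.56 at 0.2. That is smaller for some shapes, but below the uncut figure throughout.

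**The case against.** The strongest objection is scope. The sentence closes a paragraph on descriptive statistics and simple tests, and the regression paragraph that follows has no normality step. The term continuous variables may also cover covariates, and a birth count is not obviously continuous. This stands as a limit: a reader might infer that the rule is certain to be applied to births, but the text does not say so. Equally, it exempts no outcome, and it directly follows the sentence that sets sidedness for the main analyses.

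A reader might also infer that the trial's power is lost. The documents do not support that. The rule allows a transformation as well as a category, and only the category costs power. At the stated effect of 0.5 births, even the worst cut-point examined leaves 0.91. The other outcome used for sizing, contraceptive prevalence, is binary.

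Third, categorising birth spacing need not be arbitrary. The Introduction cites a 24-month recommendation, and the Discussion lists short birth intervals among the key outcomes. That is right, and such a category would be sound if fixed beforehand. The rule, however, ties categorisation to a normality test and not to that threshold.

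Finally, details of test and transformation commonly sit in a fuller plan, and the article mentions a preanalysis plan that is not shown. That plan may narrow the rule. The point made here is about a rule that is stated, not about missing detail.

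**Conclusion.** The concern holds in conditional form. As written, the rule can replace mean births, and the primary birth-spacing outcome, with an unspecified form chosen after the data are seen. If it is applied to them, rejection of normality at about 1669 women is very probable, though for a near-normal count it depends on the test used.

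The main consequence, under either branch, is a changed estimand and avoidable analyst freedom. Loss of power is secondary and arises only with categorisation. It is modest at 0.5 births and substantial at 0.2-0.3 births, where Table 4 claims 0.61 and 0.89. These sizes rest on the assumed distributions and cut-points.

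It would go too far to say that raw means are best for every outcome. Women entered the trial either pregnant or within 6 months of a birth, and the next interval is incomplete for anyone without a further birth by follow-up. A plain mean difference is therefore not clearly the right analysis for time since the last birth.

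**What to change.** - Remove the normality-test rule for outcomes.
- Analyse number of births on its original scale as a mean difference between arms, with robust standard errors clustered on the woman. This matches Table 4.
- Analyse birth spacing in a form fixed in advance, for example time to next pregnancy or birth, or the 24-month threshold that the article itself cites.
- Limit transformations to outcomes named in advance, such as income or expenditure, and report them as sensitivity analyses.

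The cost is replacing one sentence in the Analysis Plan and adding a short statement on birth spacing. No new data are needed. Dropping the rule costs the comparison of mean births no validity at this sample size (step 3). Since follow-up is complete, the revised text should be dated and should say whether outcomes by arm had already been examined.
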